### Collection of feasibility data

In order to inform a larger trial, we will collect data on:Recruitment ratesData completion ratesIntervention completion ratesAverage length of support sessionsAcceptability of the interventionTime taken to complete measures

### Qualitative analysis

We will interview children and young people and their families and clinicians about their experiences of the study and the intervention, including suggestions for improvement. These data will be analysed thematically.

## Ethics and dissemination

### Ethical approval

This study has been reviewed and approved by the Camden and Islington Research Ethics Committee (registration number 14.LO.1353). All participants will receive verbal and written information about the study, and all patients must give written informed consent before inclusion and randomisation. The study has been registered with the Current Controlled Trials register (ISRCTN21184717).

### Informed consent

Participants will be informed that their participation is voluntary and that they can withdraw at any time without providing a reason and without their medical care or legal rights being affected. Participants will be given the opportunity to ask any questions, and only when all of their queries have been answered will consent/assent be taken by the principal investigator or a suitably qualified delegated member of the research team. The participant’s informed consent will be obtained from all parents and/or carers of children taking part in the study. Where possible, older children and young people will provide informed consent and younger children will provide informed assent.

### Ethical and safety considerations

It is possible that the questionnaires, assessment and intervention may cause participants and/or carers to become distressed. The research team is made up of a number of clinically trained researchers, who will be well-placed to manage this distress should it arise and to signpost to sources of support (such as local mental health services) if necessary. Some participants will be randomised to remaining on the waiting list. However, all children will eventually receive the guided self-help intervention. We are not depriving any children of an intervention that they would otherwise have received.

### Patient confidentiality and data protection

Patient identifiable data, including initials, date of birth and NHS number will be required for the registration process. The study team will ensure that the participants’ anonymity is maintained. The participants will be identified only by initials and a participant ID number on the case report form (CRF) and any electronic database. All documents will be stored securely and will be accessible only by study staff and authorised personnel. The study will comply with the Data Protection Act, which requires data to be anonymised as soon as it is practical to do so.

### Dissemination plan

During the study, a public website will be launched and made available to participants and the health care professionals involved. It will include information and updates about the progress of the study. The results will be published in peer-reviewed scientific journals and will be disseminated at relevant research conferences and via internal reports. Written feedback will be provided to patient support groups.

## Discussion

This is the first study to investigate guided self-help interventions for mental health problems in children with neurological conditions — a group which is currently under-represented in mental health research. The intervention is modular and adapted from an empirically supported cognitive behavioural treatment. The generalisability and broad inclusion criteria are a strength but may also lead to some weaknesses, including the possibility of a child not having a confirmed neurological diagnosis and no standardised measure of physical health. In addition, this initial study will be based within a specialist hospital, which may limit generalisability. However, it also has a number of strengths, including random allocation and blinding of study assessors, enhancing internal validity of the results. It aims to be as generalisable to routine clinical practice as possible and has minimal exclusion criteria. In addition, the outcome measures used are those used in UK National Child and Young Persons Improving Access to Psychological Therapies (CYP-IAPT) services, allowing results to be compared to those across Child and Adolescent Mental Health (CAMH) services nationally.

We anticipate the study will yield important information on the feasibility of a large-scale study to assess the clinical and cost-effectiveness of guided self-help for common mental health disorders in the context of neurological illness.

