One way of meeting a large need for psychological therapy is through the use of guided self-help interventions. A recent meta-analysis of psychotherapy for depression and anxiety disorders in adults found that guided self-help interventions and face-to-face interventions are equally efficacious. A second systematic review demonstrated that the use of guided self-help interventions may be effective in adults with physical health problems [25], and such interventions including guided self-help and computerised CBT are recommended for adults with long-term physical health conditions and depression [26]. Guided self-help interventions have been shown to be beneficial in reducing symptoms of anxiety, depression and behavioural problems in children without physical illness [27–32]. Parent-delivered self-help interventions are appropriate for children aged 7–12 years old [29–31], whereas self-help conducted directly with the patient is recommended for those aged 13 and older [32, 33]. Guided self-help may be especially beneficial to people with physical illnesses, due to their potential difficulties in travelling to appointments. Additionally, children with neurological conditions are likely to have multiple medical appointments and must also attend school, and scheduling a time to meet with a therapist may be difficult in this context.

There has been no research to date examining the efficacy of self-help interventions in reducing symptoms of common mental health disorders in children with neurological conditions. The aim of this research is to conduct a pilot study to investigate the efficacy of guided self-help for symptoms of common mental health disorders in children with neurological conditions, in a preliminary randomised controlled trial (RCT) design. Compared to a waiting list control, we anticipate that children who receive guided self-help will demonstrate clinically significant reductions in anxiety, depression and disruptive behaviour, through parent-report measures (primary outcome measures). We also predict that following completion of guided self-help, children will demonstrate improvements in quality of life, also through parent-report measures.

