### Intervention

#### Guided self-help arm

The guided self-help is based on the Modular Approach to Therapy for Children with Anxiety, Depression, Trauma, or Conduct Problems (MATCH-ADTC) [37]. This combines modules for the treatment of anxiety, depression and behaviour problems, taken from known evidence-based protocols, with an empirically derived algorithm for making decisions regarding which module should be used and when. It is particularly suitable for populations with significant comorbidity, as is seen in young people with epilepsy and other neurological conditions. The main techniques that will be used are parent-delivered CBT for anxiety, problem solving for depression and parent training approaches for externalising difficulties. The adapted treatment package has been piloted with six children and young people with co-occurring mental health problems and neurological disorders. The treatment package has been revised and updated based on the findings of this pilot data and from feedback from children, young people and their families. For example, following feedback from families that one of the worksheets in the section on intervention for behavioural difficulties was confusing, this worksheet was removed from the self-help materials.

In line with previous research, the guided self-help will take the format of one face-to-face assessment and 10 telephone sessions over 12 weeks.

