### Outcome measures

#### Strengths and Difficulties Questionnaire

The Strengths and Difficulties Questionnaire (SDQ) [38] is a 25-item psychometrically robust questionnaire used for the identification of common mental and behavioural symptoms in young people. The SDQ is one of the most widely used measures of childhood psychopathology in the UK. It has been chosen as the primary outcome measure since it measures depression, anxiety and behavioural difficulties and can therefore be used by the entire sample. It has excellent reliability and validity [38].

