### Randomisation, blinding and code-breaking

Participants identified by the DAWBA and clinical assessment as experiencing impairing symptoms of mental health disorder and neurological conditions will be randomised to (1) guided self-help for their mental illness over 12 weeks or (2) remaining on the waiting list for guided self-help with no additional intervention over 12 weeks. Stratified by type of mental health disorder (anxiety, depression or disruptive behaviour), participants will be randomised 1:1 to the treatment arms using random blocks. An independent researcher will provide the randomisation codes, hold them and break the code following completion of the trial.

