### Statistical analysis

#### Primary endpoint efficacy analysis

As a pilot, the study is not powered to detect a statistically significant difference between the intervention and waiting list groups. Instead, we will use the results to estimate the effect size of the difference in order to inform a power calculation for a planned full-scale RCT. All analyses will be carried out on an intention-to-treat basis and will be blind to treatment assignment. Treatment groups will be descriptively compared on all baseline measures. No interim analyses are planned, but outcome at the end of treatment will be evaluated prior to data lock for follow-up data. The primary analysis will use the end-of-treatment SDQ assessment to compare the intervention and waiting list control groups. A linear regression adjusting for baseline assessment of the SDQ and other baseline measures for which imbalance is evident will be used to evaluate the intervention effect. Whilst we recognise that the SDQ is not as sensitive at detecting change as other measures such as the RCADS, it is the only measure which is able to detect change across all of the symptoms addressed within the study (anxiety, depression and behavioural difficulties). As diagnosis may be an important moderator of treatment outcome, we will conduct sensitivity analyses by analysing young people with confirmed epilepsy diagnoses (assumed to be the largest subset of participants) separately.

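### Assessor blinding is listed as a strength for internal validity, but the primary outcome is reported by parents who know the allocation, so it gives no protection against reporting bias in the primary result

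*Protocol article*

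**What the plan says.** The Discussion names as strengths "including random allocation and blinding of study assessors, enhancing internal validity of the results". The weaknesses in the same paragraph are the possible lack of a confirmed neurological diagnosis, the lack of a standardised physical health measure, and the specialist setting. Unblinded outcome reporting is not among them.

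The Background predicts "reductions in anxiety, depression and disruptive behaviour, through parent-report measures (primary outcome measures". The SDQ section says of that questionnaire: "It has been chosen as the primary outcome measure since it measures depression, anxiety and behavioural difficulties". The Primary endpoint efficacy analysis section fixes the comparison: "The primary analysis will use the end-of-treatment SDQ assessment to compare the intervention and waiting list control groups".

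The comparator, under Study design, is a 12-week waiting list during which nothing is added to usual care. The active arm has a face-to-face assessment and 10 telephone sessions. On content, the Guided self-help arm section says: "The main techniques that will be used are parent-delivered CBT for anxiety, problem solving for depression and parent training approaches for externalising difficulties".

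The Methods describe two masking steps. An independent researcher holds the randomisation codes (Randomisation, blinding and code-breaking), and analyses are masked to allocation (Primary endpoint efficacy analysis). The latter section also says that the effect size will feed the power calculation of a full-scale trial.

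**The concern.** Assessor blinding protects an outcome when the assessor supplies the rating. Here the parent supplies it, and the parent cannot be unaware of the arm. A parent who has put 12 weeks of work into a programme may see or report more improvement. A parent still waiting for help may report less. Both tendencies would most plausibly favour the intervention.

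Two things are at stake. A reader of the Discussion would credit the primary result with a protection that it does not have. And the effect size, which is a main product of this pilot, would go into the next trial's sample size without a warning that part of it may be reporting bias.

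**Working it through.** This is mainly a matter of setting the sections side by side.

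1. **Who supplies the primary rating?** The Background says parents. The SDQ is a 25-item questionnaire. At screening it is completed on computer, at home or in clinic (Screening and eligibility assessment). At end of treatment it comes within the DAWBA, also computerised (End-of-treatment assessment; DAWBA section). No section describes a study assessor scoring it.
2. **Does the parent know the arm?** The article does not say so, but the design leaves no alternative: one arm gets telephone sessions and the other is told to wait. The supporters who deliver the sessions also know.
3. **Is the parent part of the treatment?** Often. Anxiety is treated by parent-delivered CBT and behaviour problems by parent training. The Background regards parent delivery as suitable at ages 7–12 and direct work with the patient as recommended from 13, so this does not apply to every family.
4. **Which protections remain?**

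| Source of bias | Safeguard in the article | Covers the primary SDQ? |
|---|---|---|
| Selection into arms | Random allocation, codes held independently | Yes |
| Analyst's choices | Analyses masked to allocation | Yes |
| Outcome reporting | Assessor blinding | No: the parent is the rater |

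**Effect on the planning figure.** The only sample size in the article is the 18 from the recruitment funnel: 2755 × 2/3 × 0.85 × 0.75 × 0.50 × 0.10 × 0.66 × 0.60 × 0.75 = 17.4 unrounded, or 18 with the article's stepwise rounding. This reproduces, and the present point does not change it. The article gives no SD, effect size, alpha or power, so the rest is illustration under assumed values.

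If the true standardised effect is d and reporting bias is b, the pilot estimates d + b. For two-sided alpha 0.05 and 80% power, n per arm = 2 × (1.96 + 0.84)² / effect² ≈ 15.7 / effect², rounded up:

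| Effect used for planning (SD) | n per arm |
|---|---|
| 0.8 | 25 |
| 0.7 | 33 |
| 0.6 | 44 |
| 0.5 | 63 |
| 0.4 | 99 |
| 0.3 | 175 |

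With a true effect of 0.5 and an assumed bias of 0.1, 0.2 or 0.3, the pilot would on average point to 44, 33 or 25 per arm instead of 63. With a true effect of 0.3 it would point to 99, 63 or 44 instead of 175.

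**Can the pilot detect the bias?** No. With 9 per arm the unadjusted standard error of a standardised difference is about √(2/9) = 0.47, larger than any bias considered here. No outcome in the article is stated to be free of the bias either.

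**The case against.** The strongest reply is that the Discussion sentence credits randomisation and assessor blinding together, for the results in general, and never says that the parent-rated SDQ is protected. The DAWBA generates psychiatric diagnoses and is repeated at end of treatment, so a blinded clinician's rating could matter there. A condensed article may also omit a blinded assessor whom the full protocol describes. This stands as far as it goes: the statement is unqualified rather than shown to be false, and it would be wrong to infer that nobody is blinded. It does not rescue the primary result, because a blinded assessor elsewhere does not change who completes the SDQ.

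It is also fair to say that a parent-rated outcome against a waiting list is a defensible choice for an unpowered pilot, and that the SDQ is justified as the one measure usable across the whole sample. The point asks for an accurate description, not a redesign.

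Three stronger readings are tempting, and the documents do not support them.

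- **The code-break timing is contradictory.** The article says "An independent researcher will provide the randomisation codes, hold them and break the code following completion of the trial", yet also that "outcome at the end of treatment will be evaluated prior to data lock for follow-up data". The two are compatible: end-of-treatment outcomes can be compared under masked arm labels, as the commitment to masked analysis implies. Families knowing their own arm does not conflict with keeping the codes from the analyst.
- **The next trial would lose a definite share of its power.** This needs assumed values for both the effect and the bias, and a future trial free of the same bias. The article does not say how that trial will measure its outcome. If it repeated parent report against a waiting list, the same bias would recur, and the harm would be a biased estimate rather than lost power.
- **Child report from age 11 could serve as a check.** The children know their arm as well, and only part of a sample of 18 would supply it. It cannot detect expectancy bias.

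**Conclusion.** The concern holds as an overstated design property. Assessor blinding gives the primary result no protection against reporting bias, because the rater is a parent who knows the allocation and often takes part in the therapy. Randomisation and masked analysis keep their value against selection and analyst bias, and assessor blinding may still serve any clinician-rated diagnosis, which is not the primary outcome.

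The conclusion rests on the article's own statement that the primary measures are parent-reported, and on the inference that a waiting-list design cannot conceal the arm from families. The size of the bias is not estimable from the article. The sample sizes above show only how sensitive the planning figure is and do not measure the harm. The matter should be corrected, since it affects what may be concluded from the effect size that the pilot is meant to deliver.

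**What to change.** 1. **Limit the blinding statement** in the Discussion, and in the trial report, to the steps actually blinded: the analysis, and any clinician-rated DAWBA diagnosis if its rater was blinded.
2. **State the limitation.** Suggested wording: Families and therapists were not blinded to allocation. The primary outcome, the SDQ, was reported by parents, many of whom delivered or received the intervention, so blinding does not protect it from reporting bias.
3. **Treat the pilot effect size as possibly inflated.** When planning the full trial, show the sample size over a range of effects smaller than the pilot estimate, as in the table above, and say whether that trial's primary outcome will carry the same bias.

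No new data or change to the trial's conduct is needed. The cost is a weaker stated strength and a less favourable planning figure for the full trial.

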## Trial status

Recruitment began in January 2015 and recruitment to the study is due to end in January 2016 with all participants completing follow-up by August 2016.
